### Randomization

A randomization sequence will be generated using computer software. Stratified randomization by stop smoking advisor with blocking within each stratum will be used to ensure balance. The blocks will be randomly ordered blocks of 2, 4 and 6. Participants will be randomized 1:1 to usual care or Slimming World with usual care after they have consented to take part in the study. Stop smoking advisors, who are unaware of the randomization sequence, will open sealed, numbered, opaque envelopes in turn, after consent and initial procedures to determine allocation. Online or telephone randomization is not practical in many smoking cessation clinics because they do not have access to computers and operate outside of normal office hours.

## Interventions and comparisons

### Trial treatment providers

Trained NHS stop smoking advisors will provide participants with standard smoking cessation support, which is intended to be identical in both arms of the trial. Weight control support will be provided by trained weight management counselors employed by Slimming World. Slimming World is a CWMP which follows the National Institute for Health and Care Excellence (NICE) criteria for clinical practice. It is commissioned by the NHS to provide a weight loss service to patients.

### Provision of standard NHS stop smoking support

All participants will receive standard NHS stop smoking support. This will be the withdrawal oriented behavioral support provided by NHS Stop Smoking Services, which increases the chance of a successful quit attempt by four-fold [19]. This consists of weekly behavioral support typically for 2 weeks before and until 4 weeks after quit day, focusing on key behavioral change techniques, and nicotine replacement, varenicline or bupropion are prescribed to relieve withdrawal symptoms.

Standard stop smoking treatment consists of six sessions [20]. These are pre-booked when participants contact the Stop Smoking Service. Our trial will be nested within this usual practice as described below and shown in Figure 1.

**Figure 1 F1:**
[figure not shown]
**Flow diagram showing flow of participants through trial and main procedures.** −, weeks before quitting; 0, quit week; +, weeks after quitting.

### Trial procedures

#### Session 1: pre-quit session (week −1 prior to quit day)

During the first visit, as is usual practice, all smokers will set a quit date for 1 to 2 weeks in advance and their supply of medication to help them quit will be discussed. Smokers will be given the participant information sheet explaining the trial, providing potential participants enough time for consideration between this and the next visit. The information sheet states the opportunity to take part is entirely optional and that choosing not to participate will have no bearing on receiving usual stop smoking support.

#### Session 2: quit week (week 0)

At the second visit, smokers are usually ready to quit the next day and they will be either already taking varenicline or bupropion, or provided with nicotine replacement therapy at this visit.

Smokers will be asked whether they would like to participate in the trial. Before doing so, the stop smoking advisor will go through the trial information to make sure they have understood what is involved; for example they have to agree to attend Slimming World if randomized to it and be prepared not to go to a CWMP of their own volition if they are not randomized to it.

Those who decline to take part will be invited to give a reason. Those who agree to take part in the trial will provide written evidence of consent and will then be screened for eligibility by the stop smoking advisor. Baseline measures will be taken and they will be randomized into either usual care or Slimming World with usual care. The stop smoking advisor will provide those who are randomized to the intervention with a referral to Slimming World. This is to be taken and used at the local Slimming World group to coincide as near as possible with their quit date.

Baseline measures include a questionnaire asking for each participant’s age, gender, socioeconomic status, ethnicity, religion, daily cigarette consumption, and Fagerström test for nicotine dependence (FTND) score as usually measured by Stop Smoking Services. They will also be asked to complete the EQ-5D (EuroQol, Rotterdam, Netherlands) measure of health status and report whether they suffer from type 2 diabetes mellitus.

#### Sessions 3 to 5: weeks 1 to 3 post-quit (week +1, +2, +3)

The next three sessions will provide behavioral support for quitting in both the intervention and usual care group. The intervention group will also attend Slimming World.

#### Session 6: week post-quit (week +4)

This is typically the last visit to the Stop Smoking Service and when 4-week abstinence will be assessed. Weight will be measured and the EQ-5D will be completed by all participants at this visit.

#### Session 7: 12-week follow-up (week +12)

This corresponds with the end of weight management treatment. Weight and smoking abstinence will be measured. This session is important for determining the sample size needed for the non-inferiority trial which, as is standard in stop smoking trials [21], will require a 6-month follow-up to assess long-term smoking abstinence.

#### Session 8: 26-week follow-up (+26)

If data from 12-week follow-up shows a difference in mean weight, we will include a 26-week follow-up. The numbers of individuals who will return at this point will be recorded, and weight and smoking abstinence will be measured.

### Intervention

CWMPs are available ‘on prescription’ through general practices and provide 12 weeks of free membership of the group-based weight management class. There are three main providers offering services to the NHS: Rosemary Conley, Slimming World and Weight Watchers; the cost of a 12-week course to the NHS is about £60. Each of these providers are potentially suitable and their interventions have been described elsewhere [16]. In brief, each provides goal setting for weight, regular monitoring, and a tailored energy restriction using a either a food points system (Weight Watchers), food portion measures (Rosemary Conley), or controlled amounts of high energy foods and personal eating plans (Slimming World).

For this trial, we are using Slimming World, since this provider has been successful at improving health and reducing health risks associated with specific medical conditions through referral schemes within particular patient populations, some of which are designed to prevent excessive weight gain rather than focus on weight loss, for example during pregnancy [22,23]. Such an approach is particularly pertinent to quitting smokers who need to prevent cessation-related weight gain.

In addition to usual care, participants will be given a referral form for Slimming World when they attend their pre-quit visit. The stop smoking advisor will discuss times and locations of local group meetings, and attendance at a convenient group will be agreed. The participant will attend weight management sessions from their quit day (or as near to that date as possible). They will attend Slimming World for 12 weeks receiving support to lose weight or prevent weight gain. The choice of modest weight loss or weight gain prevention will depend upon whether a participant wants to lose weight or not, and whether or not the participant is overweight or obese at baseline.

Typically, Slimming World members lose 0.3 kg/week (or 0.4 kg/week in people who complete 10 of the 12 weeks) [24]. We know that on average 0.2 kg/week is gained with smoking during the first 12 weeks of quitting [10]. Factoring in this expected change in weight resulting from quitting, we would expect a mean weight loss of 0.2 kg/week. For participants who are overweight, a theoretical minimum weight loss goal may therefore be 2.4 kg or 3/4 stone over 12 weeks, although trials to date to prevent smoking cessation weight gain have not achieved as much as this (Table 1). Slimming World consultants typically agree weight loss targets with their members at the first appointment, so appropriate targets will be negotiated on an individual level within realistic margins. Slimming World consultants then work with their members to achieve this.

For participants whose starting BMI is 23 kg/m^2^, for example a 60 kg woman with a height of 1.62 m, the weight loss of 2.4 kg described above would result in a BMI of no less than 22 kg/m^2^, which is in the optimum range for longevity; this is why we have chosen a BMI less than 23 kg/m^2^ for our exclusion criteria.

Most people attending Slimming World do so with weight loss as their goal. For participants in this study who are only seeking to prevent further weight gain, they will be reassured that weight maintenance (+/−0.5 kg over 12 weeks (see section on sample size)) is an equally worthwhile target during smoking cessation and the participant information sheets for the trial will clearly explain this.

### Control

Participants are encouraged to quit smoking first, before tackling weight. Stop smoking advisors can advise satiating hunger with healthy foods, but they will not provide detailed or personalized advice on weight and will not set weight targets.

## Outcome measures

### Primary outcome measure

Change in weight from baseline to 12 weeks post-quit day in abstinent smokers. Abstinence is prolonged abstinence, defined according to the Russell Standard as self-report of no more than five cigarettes since 2 weeks following quit day and expired CO less than 10 ppm [21]. Portable validated scales will be provided to participating Stop Smoking Services. Training in measurement procedures and the trial protocol will be provided for all advisors. The same scales will be used at each clinic at all time points. All measures will be recorded on paper case report forms (CRFs) and later entered into a trial database.

### Secondary outcome measures

• Weight at 4 weeks post-quit date.

• Weight at 6 months from baseline.

• Abstinence at 4, 12 and 26 weeks. Abstinence will be defined as not smoking more than five cigarettes since 2 weeks after the quit day verified by expired CO <10 ppm at these visits (Russell Standard criteria). Abstinence will be recorded on the CRF and in the trials database.

• Participant acceptability.

#### Participant acceptability

Participant acceptability will be measured quantitatively by response, attrition rates and a questionnaire as described below:

• Rates of response to verbal invitation to take part by stop smoking advisors, including reasons for declining to participate.

• Rates of attendance at the commercial weight management meetings by participants randomized to this intervention.

• Rates of drop out from Stop Smoking Services in intervention compared to usual care.

• Rates of attendance at Stop Smoking Services for follow-up at 12 and 26 weeks.

• The above measures of acceptability according to starting BMI; for example are participants who are obese or overweight more accepting of the intervention which refers to Slimming World than those of a healthy weight?

• A questionnaire will be given to participants who decline to take a part, which will ask them to provide their age, gender, ethnicity, weight status, and reason(s) for declining using a series of closed answer responses (for example: ‘I do not want to take part in research’, ‘I do not think the intervention will work’, ‘I do not want to lose weight’) and one open ‘other’ category.

• All participants who drop out of treatment or follow-up will be asked, if they are willing, the reason for discontinuing using a series of closed answer responses (for example: ‘it was too hard to quit smoking’, ‘it was too hard to lose weight’, ‘I did not like the allocation I received’) and one open ‘other’ category.

#### Feasibility

Feasibility of running the trial within the Stop Smoking Services will be assessed by questionnaire. Participating services will be asked to rate the ease of adhering to the research procedures and describing any difficulties encountered, such as problems with recording data.

### Exploratory outcomes measures

• Self-reported incidence of diabetes.

• Change in EQ-5D.

• Cigarette withdrawal symptom scores as measured by the mood and physical symptoms scale (MPSS) [25].

• Associations of change in religious engagement (adapted from CSI-MEMO [26]) and religious coping (religious coping index (RCI) [27]) at baseline, and their change over time with tobacco withdrawal, quitting success and weight maintenance outcomes.

A recent systematic review of observational studies shows less smoking is associated with religion. Also, despite a higher BMI, religious involvement is associated with better physical and psychological outcomes [28]. The use of religion as a means to cope with health problems is a potential mechanism behind this association [27].

Clinical trials comparing weight loss interventions with a religious element to those without have shown increased physical activity [29], improved dietary quality [30] and greater mean weight loss [31,32] in participants receiving the additional religious element. Survey and qualitative data suggest smokers [33] and those who overeat [34] are receptive to incorporating a spiritual element into treatment programmes.

Although this evidence suggests a beneficial association and an openness to addressing spiritual needs in those who need to lose weight and stop smoking, many of these studies have been carried out in the Bible Belt, USA, and their applicability to the UK population needs to be determined.

## Statistics and data analysis

### Sample size

A meta-analysis of studies shows that smokers who achieve 12 weeks of abstinence gain around 2.5 kg (SD = 2.5) [10]. A Cochrane review to prevent weight gain when people stop smoking [15] showed that at 4 and 52 weeks post-quit there was a difference of 1.1 kg and 2.6 kg, respectively, between usual care and individualized dietary intervention (Table 1). This means that individualized dietary interventions prevented most of the expected weight gain at 4 weeks post-quit and half of it at 1 year post-quit. A realistic estimate is therefore that we may be able to prevent 80% (2 kg) of the expected weight gain at 12 weeks post-quit, that is the intervention group might gain only 0.5 kg on average. This would require about 32 participants per arm, 64 participants in total, with an alpha error rate of 5% and 90% power. Most smokers who attempt abstinence will relapse to smoking, probably lose any weight gained [9,31] and will not be included in the primary outcome assessment. Considering that approximately only 20% will remain abstinent at 12 weeks, we will need to randomize 160 participants in each trial arm and 320 participants overall.

### Analysis plan

#### Primary analysis

Change in weight between intervention and the control arm of the study will be compared using a *t*-test and then adjusted for known predictors of weight gain after cessation, including stop-smoking medication use, using linear regression analysis. Weight will be analysed in long-term abstainers because only long-term abstainers gain more weight over time than the rest of the population.

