**Methods:**

This RCT will examine the effectiveness of usual cessation support plus referral to Slimming World compared to usual cessation support alone. Healthy weight, overweight and obese adult smokers attending Stop Smoking Services will be included. The primary outcome is weight change in quitters 12 weeks post-randomization. Multivariable linear regression analysis will compare weight change between trial arms and adjust for known predictors of cessation-related weight gain.

We will recruit 320 participants, with 160 participants in each arm. An alpha error rate of 5% and 90% power will detect a 2 kg (SD = 2.5) difference in weight gain at 12 weeks, assuming 20% remain abstinent by then.

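### The primary outcome is to be analysed by an unadjusted t-test and by an adjusted regression, and the protocol does not say which result decides

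*Protocol article*

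**What the plan says.** The protocol article describes the primary comparison in three places.

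- **Primary analysis section:** "Change in weight between intervention and the control arm of the study will be compared using a *t*-test and then adjusted". The adjustment is for "known predictors of weight gain after cessation, including stop-smoking medication use, using linear regression analysis". Medication use is the only predictor named.
- **Abstract, Methods:** "Multivariable linear regression analysis will compare weight change between trial arms and adjust for known predictors of cessation-related weight gain". The t-test is not mentioned.
- **Sample size section:** 2 kg difference, SD 2.5, 5% alpha and 90% power give about 32 per arm. At 20% abstinence this becomes 160 randomised per arm. No allowance is made for covariates.

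The outcome is "Change in weight from baseline to 12 weeks post-quit day in abstinent smokers". On allocation, the Randomization section says "Stratified randomization by stop smoking advisor with blocking within each stratum will be used to ensure balance". Advisor does not reappear in the analysis plan, and baseline weight is not named as a covariate anywhere.

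The Session 8 text makes the 26-week visit conditional on a difference in mean weight at 12 weeks. The Background makes the application for a non-inferiority trial of over 1,100 participants conditional on the intervention reducing weight gain.

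**The concern.** Two estimates and two p-values will exist for one primary question, and the article does not rank them. The analysis section can be read as t-test first with regression in support. The abstract reads as regression only. In an analysis set of about 64 people, chance imbalance in a prognostic covariate can put the two results on opposite sides of 0.05. The article would then give no agreed answer to the question on which the 26-week follow-up and the larger trial depend.

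There is also a cost in precision. If the t-test decides, the trial does not use covariate information that it already holds, in an analysis set that is only about one fifth of those randomised.

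**Working it through.** **1. Which test is the sample size built for?** Inputs from the Sample size section: difference 2 kg, SD 2.5, alpha 5% (taken as two-sided), power 90%.

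n per arm = 2 × [2.5 × (1.960 + 1.282) / 2]² = 32.8, so 33. The exact t calculation gives 34; a one-sided test would give 27. The stated figure of about 32 is therefore reproduced, to rounding, as an unadjusted two-sided comparison, and 32 / 0.20 = 160 per arm. The sample size is not in error here. It matches the t-test and not the regression that the abstract names.

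**2. Power at 32 per arm.** The noncentrality is 2 / (SD × √(2/32)) = 2 / (SD × 0.25). For the adjusted test the SD becomes 2.5 × √(1 − R²), where R² is the share of variance in weight change explained by the covariates. The article gives no R², so the values are assumptions. The few degrees of freedom spent on covariates are ignored.

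| Assumed R² | Residual SD | Noncentrality | Power |
|---|---|---|---|
| 0 (t-test) | 2.50 | 3.20 | 88.3% |
| 0.05 | 2.44 | 3.28 | 89.8% |
| 0.10 | 2.37 | 3.37 | 91.3% |
| 0.20 | 2.24 | 3.58 | 94.1% |

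**3. How often could the two tests disagree?** This uses 20,000 simulated trials with no true effect, 32 per arm and four covariates (an assumption). The share in which exactly one test is significant is 2 × P(either) − P(t-test) − P(regression).

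| Assumed R² | P(t-test) | P(regression) | P(either) | Exactly one significant |
|---|---|---|---|---|
| 0.10 | 0.0503 | 0.0494 | 0.0668 | 0.0339 |
| 0.20 | 0.0499 | 0.0503 | 0.0726 | 0.0450 |
| 0.30 | 0.0523 | 0.0493 | 0.0789 | 0.0562 |

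Each test alone holds its 5%. Only a rule that accepted either one would take type I error to about 6.7–7.9%.

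**4. Does leaving out advisor make the t-test invalid?** With perfect balance in 16 advisor strata of four people (an assumption), the t-test's type I error is about 0.049, 0.046, 0.040 and 0.031 at an advisor intraclass correlation of 0, 0.05, 0.10 and 0.20.

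The real analysis set will be less balanced, because only about 20% of each block is retained. Simulating 320 people randomised in blocks of 2, 4 and 6 within 8 to 40 advisors, with a random 20% kept, gives 0.045 to 0.054. A repeat gave mostly 0.045 to 0.055, with 0.037 in the most clustered case. The direction is towards a conservative test, and the effect is small.

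**The case against.** The strongest reply is that a crude comparison followed by an adjusted one is an ordinary sequence. The analysis section puts both in one sentence, and the abstract merely names the last step. The sample size supports the t-test as the powered comparison. A covariate list and the form of the model are commonly left to an analysis plan, which is not shown. The trial is a phase II step before a larger one.

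Much of this stands. An open covariate list would not be a finding by itself. What remains is within the article: the abstract and the sample size point to different tests, and no sentence ranks them. Reading the t-test as primary is possible, but the abstract contradicts it.

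Four stronger inferences are tempting, and the document does not support them.

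- **That the t-test ignores baseline weight altogether.** The outcome is change from baseline, so baseline weight is already subtracted. Only a covariate term for it is unnamed, and the open list of predictors might include one.
- **That type I error is inflated to 7% or 8%.** This needs a rule that either test may claim success, and the article states no such rule.
- **That ignoring the advisor strata produces false positives.** Step 4 shows the opposite direction, and little effect once about 80% of those randomised leave the analysis set.
- **That the secondary weights will be analysed raw.** "Weight at 4 weeks post-quit date" is an outcome label. The Secondary analysis section does not describe how those weights will be compared.

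**Conclusion.** The point holds in a limited form and is of moderate importance. The article plans two analyses of its primary outcome and does not say which decides. Its abstract favours the regression and its sample size the t-test. With no true effect, the two would fall on opposite sides of 0.05 in roughly 3% to 6% of trials, at assumed R² of 0.10 to 0.30 with four covariates.

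Relying on the t-test would mean 88.3% power, where an adjusted model would give about 91% or 94% at assumed R² of 0.10 or 0.20. The gain vanishes if the covariates explain nothing. The 88.3% is within rounding of the planned 90% and is not a fault in the sample size. Naming one adjusted model is therefore a low-cost improvement that also settles the ambiguity; it does not repair an invalid test.

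**What to change.** State in the same words in the abstract and in the Primary analysis section that the primary analysis is a linear model of 12-week weight change on arm, with:

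- baseline weight as a covariate;
- a short, fixed list of predictors measured before randomisation, for example sex and either the Fagerström score or daily cigarette consumption;
- stop smoking advisor as a random intercept, which reflects the stratification without spending a degree of freedom on each advisor.

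State that this model's treatment effect decides the primary question and that the unadjusted t-test is supportive only. If medication use stays in the list, define it as the medication chosen before allocation, so that it cannot be affected by arm. Fix the list before outcome data are seen.

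The cost is a change of wording. Gender, cigarette consumption and the Fagerström score are among the listed baseline measures, baseline weight is needed for the outcome itself, and advisor is known from randomisation. The sample size need not change.

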## Background

Weight gain is a well known consequence of smoking cessation [1,2]. It may deter smokers from attempting to quit [3] and offsets some advantages of giving up smoking. Smoking cessation-related weight gain partly explains the finding that the incidence of type 2 diabetes is increased by up to 73% in the years after cessation [4-6] and there is a 30% increased risk of hypertension [7] compared to continuing smoking. Quitters who gain weight have less improvement in lung function than those who avoid weight gain [8].

An ideal intervention to prevent weight gain would begin at the time of quitting, because weight gain is most rapid initially and then the rate of gain slows [9,10]. Qualitative findings suggest that, in the overweight population, at least, waiting until a quit attempt is established before addressing weight is unacceptable [11].

However, preventing weight gain early in cessation is controversial. The main reason quit attempts fail is due to quitters succumbing to their cravings to smoke. Evidence suggests that hunger increases urges to smoke [12,13] and people who gain most weight are more likely to succeed in quitting smoking [14]. This suggests that avoiding hunger and ameliorating cigarette cravings with food may enhance smoking abstinence and this has become standard advice on how to quit, with healthy food choices often advocated.

We investigated the effectiveness of different interventions to prevent weight gain during cessation in a recent Cochrane review update [15]. General dietary education to reduce energy intake through eating a low fat, healthy diet and increasing exercise did not prevent weight gain compared to standard smoking cessation behavioral support. Furthermore, there was a statistically significant reduction in abstinence at 12 months (Table 1). However, an individually tailored plan to reduce energy intake and increase exercise, with regular monitoring and adaptation of individual goals, reduced weight gain at 6 and 12 months without a statistically significant reduction in abstinence rates (Table 1), although the sample size is too small to be conclusive.

**Table 1 T1:** Effects of dietary interventions on weight change and abstinence during smoking cessation

**Intervention compared to standard smoking cessation**	**Mean difference in weight change (kg (95% CI))**		**Abstinence (RR (95% CI))**	
	**End of treatment**	**At 12 months**	**End of treatment**	**At 12 months**

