## Methods

### Design

This is an open label, phase II, randomized controlled trial (RCT) to compare standard stop smoking behavioral support with an intervention that will, in addition to providing standard stop smoking support, include personalized weight management support, provided by Slimming World.

This is an open label trial, so blinding patients and smoking cessation advisors to allocation to intervention or control is impossible. The primary outcome is objectively measured weight and therefore the scope for bias is limited. Stop smoking advisors, who will weigh participants, will not provide the weight control support and are unlikely to have a vested interest in interpreting weight change favorably. In addition, they will be required to follow a protocol that specifies outdoor coats and shoes only are removed before weighing.

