### Loss to follow-up

In accordance with the Russell Standard, we will conduct an intention-to-treat analysis and assume participants lost to follow-up are smokers. We will attempt to contact participants who do not attend. Reminder phone calls will also be made before 12-week and 6-month follow-up appointments.

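### The primary week-12 weight comparison is confined to attending, CO-verified abstainers, a group formed after randomisation, and no all-randomised week-12 weight comparison is described beside it

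*Protocol article*

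**What the plan says.** The Primary outcome measure section defines the endpoint as "Change in weight from baseline to 12 weeks post-quit day in abstinent smokers". Abstinence there means "self-report of no more than five cigarettes since 2 weeks following quit day and expired CO less than 10 ppm", so a participant must attend and give a breath reading to count. The Loss to follow-up section says the team will "assume participants lost to follow-up are smokers", which places non-attenders outside the abstainer group. The Sample size section says openly that relapsers are left out of the primary outcome.

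The reason given for the restriction is: "Weight will be analysed in long-term abstainers because only long-term abstainers gain more weight over time than the rest of the population". The planned analysis is a t-test followed by linear regression on known predictors of weight gain, including cessation medication.

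On bias, the Design section argues: "The primary outcome is objectively measured weight and therefore the scope for bias is limited". In the Background, the case against early weight control is that hunger increases urges to smoke and that "people who gain most weight are more likely to succeed in quitting smoking".

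At the week-12 visit (Session 7), "Weight and smoking abstinence will be measured", with no restriction to abstainers. The secondary outcomes include weight at 4 weeks and at 6 months, with no population stated. The Secondary analysis section applies intention-to-treat to abstinence.

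**The concern.** Randomisation makes the two sets of 160 comparable. It does not make the two subsets of abstainers comparable if allocation affects who stays abstinent and if staying abstinent is related to weight change. The protocol's own Background supplies both links. A difference in mean weight change between the subsets could then come partly from who is in them.

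The stated rationale explains where a weight effect is expected. It does not address whether abstainers in the two arms remain alike. The objectivity argument covers how weight is measured, not who enters the analysis. Regression on known predictors corrects only for the differences those predictors capture.

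The week-12 result decides whether the 26-week follow-up takes place (Session 8 and Trial closure) and whether funding is sought for a further trial of over 1,100 participants (Background). The abstract and Discussion say the trial will establish whether referral is an effective way to prevent cessation-related weight gain.

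**Working it through.** **Inputs.** From Sample size: target difference 2 kg (gain of 0.5 against 2.5 kg), SD 2.5 kg, alpha 5%, power 90%, 20% abstinent at 12 weeks, 160 per arm. From Table 1, individually tailored advice: abstinence RR 1.11 (0.84, 1.46) at end of treatment and 0.74 (0.39, 1.43) at 12 months. Assumed here: two-sided alpha and normally distributed weight change.

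**1. The plan's own figure.** n per arm = 2 × [SD × (1.960 + 1.282) / 2]² = 2 × (2.5 × 3.242 / 2)² = 32.8, against about 32 in the plan. Then 32 / 0.20 = 160 per arm, 320 in all. The figure reproduces. It takes abstinence as 20% in both arms and treats the abstainers as comparable.

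**2. Worst-case selection bias.** Suppose the intervention moves abstinence in one direction only. Then the arm with more abstainers contains a fraction q = 1 − min(RR, 1/RR) who would not have been abstinent in the other arm. The bias is largest when all of them lie in one tail of weight change:

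maximum bias = SD × φ(z_q) / (1 − q)

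| RR (tailored advice) | q | φ(z_q) | Maximum bias | Share of 2 kg |
|---|---|---|---|---|
| 1.11, end of treatment | 0.099 | 0.174 | 2.5 × 0.174 / 0.901 = 0.48 kg | 24% |
| 0.74, 12 months | 0.26 | 0.324 | 2.5 × 0.324 / 0.74 = 1.10 kg | 55% |

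At the end-of-treatment confidence limits (0.84 and 1.46) the same formula gives 0.72 and 1.30 kg. These are limits, not estimates.

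**3. A milder case.** If the extra abstainers differ from the others by 0.5 to 1 SD (1.25 to 2.5 kg), the bias is q times that difference:
- RR 1.11: 0.099 × 1.25 = 0.12 kg to 0.099 × 2.5 = 0.25 kg
- RR 0.74: 0.26 × 1.25 = 0.33 kg to 0.26 × 2.5 = 0.65 kg

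**4. Equal abstinence rates.** Equal rates do not exclude bias if different people abstain in each arm. With 20% abstinent in both arms, no true weight effect, and abstinence in one arm only depending on weight-gain tendency (assumed odds ratio 1.5 per SD, logistic model), the shift is 0.78 kg. The bounds in step 2 are therefore upper limits only under their one-direction assumption.

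**5. Effect on the test.** With 32 per arm the standard error is 2.5 × √(2/32) = 0.625 kg. With no true effect, a bias of 0.5 kg raises a nominal 5% two-sided false-positive rate to about 13%, and a bias of 1.1 kg raises it to about 42%. A bias in the other direction would hide a real effect.

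**6. Power of an all-randomised comparison.** If only the 20% who abstain benefit, the average effect is 0.20 × 2 = 0.4 kg. With 160 per arm and SD 2.5 the standard error is 2.5 × √(2/160) = 0.28 kg, and power is about 30%. If everyone benefited by 2 kg, power would exceed 99% at SD 2.5 and be about 95% at an assumed SD of 5. These figures take a week-12 weight for everyone.

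**The case against.** The restriction is deliberate, explained and openly stated. The trial concerns weight gain caused by quitting, people who relapse are expected to lose what they gained, and an all-randomised average would dilute the effect. That stands, and it is why the abstainer contrast can remain primary. It does not answer the loss of randomised comparability.

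Imputation and sensitivity analyses usually belong in a statistical analysis plan, which is not shown, and a journal article is condensed. That also stands, so their absence is not the point here. The point is what the article does fix: the primary population and a rationale that leaves this problem unaddressed.

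Several stronger readings are tempting but unsupported:

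- **That no weight analysis outside abstainers is planned.** The 4-week and 6-month secondary weights carry no restriction, week-4 weight is taken from all participants, and the exploratory analyses mention weight control on an intention-to-treat basis, though only for associations. What can be said is that no all-randomised between-arm comparison at week 12 is described.
- **That the plan promises intention-to-treat for weight and breaks the promise.** The sentence "we will conduct an intention-to-treat analysis and assume participants lost to follow-up are smokers" is introduced by reference to the Russell Standard and concerns smoking status.
- **That the bias could reach about 70% of the target on Table 1 figures (RR 0.66, 1.39 kg).** That ratio belongs to general lifestyle advice, which the Background contrasts with the tailored type tested here.
- **That membership of the analysis set rests on self-report alone.** The definition also requires CO below 10 ppm. This limits misclassification in an open-label trial, although a single breath reading cannot confirm the prolonged cigarette count.

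**Conclusion.** The point holds in a limited form. The primary weight contrast compares about 32 abstainers per arm, selected after randomisation on a characteristic that the protocol itself links to hunger and to weight gain. Neither the stated rationale nor the objectivity argument shows the groups to be comparable.

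Selection alone could move the contrast by at most about 0.48 kg (RR 1.11) to 1.10 kg (RR 0.74), or 24% to 55% of the 2 kg target. This rests on normal weight change with SD 2.5, a one-direction effect on abstinence, and risk ratios that do not belong exactly to week 12. Week 12 is the end of weight-management treatment, so the lower figure is the closer match, although Sample size appears to date the end-of-treatment result at 4 weeks. The higher figure uses a 12-month estimate with a wide interval.

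A reader might infer that the primary result is biased by these amounts, or that the design is invalid. The documents support neither. The figures are possible extremes, the direction is unknown, and the bias is zero if the intervention changes neither how many nor which participants stay abstinent. What follows is that the abstainer contrast should not carry the conclusion alone, and the repair is cheap.

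**What to change.** 1. Keep the abstainer contrast as the primary analysis.
2. Pre-specify a supporting comparison of week-12 weight change in all randomised participants by allocated arm, whatever their smoking status. Use the Session 7 weights, with multiple imputation of missing weights from arm, baseline weight, 4-week weight and smoking status.
3. Add a trimming-bounds sensitivity analysis of the abstainer contrast, based on the abstinence difference observed in this trial.
4. In the abstract and Discussion, limit the conclusion to participants who were abstinent, unless the all-randomised result supports the wider claim.

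**Cost.** Analysis-plan wording and a little more analysis. No new visit or measurement is needed: Session 7 already includes weight, and participants who miss treatment visits are still contacted for follow-up unless they ask otherwise. The drawback is low power, about 30% for 0.4 kg if the effect is confined to abstainers, and less with missing weights or a larger SD. A null all-randomised result would not refute the primary finding, so this analysis is supportive only.
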